#### Saliva collection (sAA and cortisol)

Salivary samples for evaluation of sAA and cortisol are collected throughout the experimental manipulation at 4 timepoints. These collection timepoints include: before cognitive testing begins/baseline, following the intervention, following post-intervention cognitive tasks, and at the completion of the visit. At each collection time, participants are seated comfortably, leaning forward with arms crossed in front of them. Unstimulated salivary samples (at least 2 mL) are collected by the passive drool technique over a 2-min period. Samples are collected into pre-weighed saliva collection tubes and immediately placed on ice. After weighing collection tubes for quantitation of saliva volume and determination of flow rate ([post-collection tube weight − pre-collection tube weight]/2 min), samples are aliquoted and frozen at − 80 °C until analysis. sAA and cortisol are packaged, shipped on dry ice, and analyzed at the University of Ottawa. sAA and cortisol are measured using commercially available kits (α-amylase Saliva Enzymatic Assay and Cortisol Saliva ELISA, IBL International, Hamburg, Germany) according to manufacturer’s instructions. Briefly, on the day of analysis, saliva samples are thawed, centrifuged at 1500×*g* for 15 min at room temperature to remove cellular contaminants and debris. For sAA, samples are diluted 1:301 in diluted sample buffer, and read in a microplate reader (POLARstar Omega, BMG Labtech, Guelph, Canada) at 22 °C at a wavelength of 405 nm at 3 and 8 min after incubation at room temperature. For CORT, samples are incubated with enzyme conjugate solution at room temperature for 2 h, washed, incubated with enzyme substrate solution at room temperature for 30 min. After the addition of the “Stop Solution” to end the enzyme/substrate reaction, samples are read in a microplate reader (POLARstar Omega, BMG Labtech, Guelph, Canada) at 450 nm within 15 min. All samples are analyzed at least in duplicate.

Children are asked not to eat a major meal; consume food high in caffeine, sugar, or acidity; or brush their teeth for at least an hour before the session. In order to control for diurnal variation, each child’s sessions are scheduled at the same time of day. They are also asked to report the presence of any oral disease or injury, and whether or not they consumed any medications within the 12 h prior to the sessions. Adherence to these protocols is confirmed before beginning any sessions. If children have not followed the pre-testing protocols, enough time is passed to allow the protocol to be followed, or the child is rescheduled. Before the first collection of each visit, participants are instructed to swallow and rinse with water to clear the mouth of all saliva. Children are then not allowed to have anything to eat or drink throughout the rest of the session. Salivary samples for evaluation of sAA and CORT are collected throughout the intervention sessions. Specifically, samples are collected at baseline (after 10 min of baseline sitting), prior to (PRE), and immediately following experimental manipulation (i.e., exercise, TSST-C, rest), ERP/cognitive testing, and academic achievement testing (see Experimental Timeline).

### Blinding and randomization

Children are randomized after they complete the first visit. Each child receives each intervention in a counterbalanced, randomized fashion. The order of the intervention occurs through block randomization. Participants are unaware of their intervention order and are not informed of what intervention they will be completing during any given session until the actual intervention begins.

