## Material and design

### Summary of aims

The objective of the SNEACY study is to test several aims: (1) Investigate basic laboratory and applied scholastic performance aspects of brain function, cognition, and academic achievement following aerobic exercise compared to active (i.e., Trier Social Stress Test for Children (TSST); a commonly used psychosocial stressor) and passive (i.e., seated rest) control conditions; and (2) Investigate phasic changes in SNS activation (as indicated by sAA) as a potential mechanism for the transient beneficial effect of exercise on brain function, cognition, and academic achievement. Phasic activation refers to brief, rapid changes in the SNS [17] in response to salient or task-relevant information in the stimulus environment [18]. Phasic sAA has been shown to be related with attention, memory, and various academic outcomes [16, 18–22]. SNEACY is a randomized crossover trial with three acute interventions: 20 min of moderate intensity treadmill exercise, 20 min of seated rest, and a 14-min TSST for Children. The TSST and seated rest interventions serve as active and passive control conditions, respectively, for the experimental intervention involving moderate intensity exercise. As a result of this design, changes observed in the aerobic exercise intervention can be attributed to the exercise component of the intervention rather than to other, potentially confounding factors, such as expectancy effects, stress, or elevated heart rate. The study will enroll and randomize 103 typically developing, 9–10-year-old children. We hypothesize that exercise-induced phasic increases in SNS activity, indicated by sAA levels, will mediate the effect of a single bout of exercise on brain function (i.e., P3 amplitude and latency), cognition (i.e., executive control), and standardized achievement test performance (i.e., mathematics, reading). To further explore a relation between exercise-induced change in sAA with brain and cognition, baseline and stress-induced (i.e., exercise, TSST) change in cortisol will be investigated as a potential factor in the analytical model. All participants provide written assent/consent (and legal guardians provide written informed consent) by a trained research technician in accordance with the Institutional Review Board of Northeastern University. The study was designed in accordance with the SPIRIT statement, details are provided in Fig. 1.

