#### Days 2–4 procedure

At intervention visits (days 2, 3, and 4), the participant engages in the same protocol each day, with the sole exception of a different intervention each day. At the start of each visit, children are outfitted with a heart rate monitor to measure the intensity of the intervention. Upon entering the laboratory, children are asked to sit quietly for 10 min to allow their heart rate to return to baseline levels, after which they provide the first saliva sample by drooling into a tube. Participants are then fitted with an EEG cap. Next, they complete cognitive tasks on a computer while EEG data is simultaneously collected. Then, the child completes one intervention at each visit: (1) aerobic exercise, (2) quiet resting, or (3) the TSST. Upon completion of the intervention, participants provide another saliva sample. Participants then complete the same cognitive tasks again while EEG data is simultaneously collected. Participants will provide another saliva sample, and then they will complete an academic achievement test. At the end of the visit, the final saliva sample is collected. Visits 2–4 last approximately 2.5 h each. At the conclusion of study participation, no further ancillary or post-trial care was offered.

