#### Interventions

Children are asked not to exercise or participate in structured physical activity prior to attending any of their sessions, and this is verified via self-report before each intervention session. Maximal heart rate (HRMax) is determined from the maximal exercise test completed on day 1 and is used to determine relative exercise intensity for days 2, 3, or 4. The interventions will be completed in a randomized crossover design, such that participants will act as their own controls, through initial randomization to condition assignment and condition counterbalancing across participants. With 3 interventions, there are a total of 6 different interventions (for example, aerobic-TSST-rest, aerobic-rest-TSST, TSST-rest-aerobic, TSST-aerobic-rest, rest-aerobic-TSST, rest-TSST-aerobic). A random number generator will be used to determine which intervention order a participant receives. See Table 2 for participant timeline.

**Table 2 Tab2:** Participant timeline

Time schedule	Activity
6–30 months	Participants Enrolled
Approximately 1 week prior to intervention 1	Day 1

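### The design does not exclude expectancy effects as the protocol claims, and a child's unawareness of the condition order cannot be assured at the last visit

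*Protocol article*

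**What the plan says.** All references are to the protocol article.

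- **Summary of aims.** The stress test (TSST) and seated rest are the active and passive controls. As a consequence of this design, changes seen with exercise are said to be attributable to exercise and not to other factors, "such as expectancy effects, stress, or elevated heart rate".
- **Blinding and randomization.** "Each child receives each intervention in a counterbalanced, randomized fashion". "Participants are unaware of their intervention order", and children "are not informed of what intervention they will be completing during any given session until the actual intervention begins".
- **Days 2–4 procedure.** "Then, the child completes one intervention at each visit", and the visits follow one protocol "with the sole exception of a different intervention each day". Children first sit quietly, "after which they provide the first saliva sample by drooling into a tube"; cap fitting, the pre-intervention tasks with EEG and then the intervention follow. Table 2 puts the baseline saliva sample after cap fitting, but still before the tasks and the intervention.
- **Primary outcome.** The primary outcomes are changes in cognitive performance after each intervention.
- **Power and analytic strategy.** Baseline sAA and cortisol, as well as sAA change, enter the path model as possible mediators of the effect of condition.

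**The concern.** Two statements about what children know and expect support the interpretation of the trial, and neither is fully earned by the design described.

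First, expectancy. A control condition removes expectancy only if participants expect as much from it as from the experimental condition. Sitting with a book and speaking before observers are easily told apart from treadmill exercise, and the article describes neither matching on expected benefit nor any measure of expectation. If children think exercise helps them perform, that belief is present at every post-exercise test.

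Second, concealment. In a complete crossover with recognisable conditions, the last condition can be found by elimination. The pre-intervention measures at that visit can then be taken while the child anticipates a particular condition. The article itself describes the TSST as meant to raise stress and as raising sAA and cortisol, so anticipating it could plausibly act on those markers. There is no such reason for anticipating rest. A raised TSST baseline would shrink the measured TSST change and could appear in the path model as an effect of condition on baseline.

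**Working it through.** **1. Number of orders.** Three conditions, each received once, give 3! = 6 orders. This reproduces the figure in the Interventions section ("With 3 interventions, there are a total of 6 different interventions", where the list that follows shows that orders are meant). Each condition is last in 2 of the 6.

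**2. What a child can infer.** Assume the child knows the three conditions and that none repeats. The chance of naming the next one is 1 divided by the number remaining:

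| Visit | Conditions remaining | Chance of naming it |
|---|---|---|
| Day 2 | 3 | 1/3 |
| Day 3 | 2 | 1/2 |
| Day 4 | 1 | 1 |

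The average is (1/3 + 1/2 + 1)/3 = 0.61.

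**3. Number of visits.** With 103 children there are 3 × 103 = 309 intervention visits. Of these, 103 are fully predictable, or 103/3 ≈ 34 per condition under balanced orders. Another 103 are narrowed to two options.

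**4. Effect on a condition mean.** Let D be the baseline shift, in SD units, when one condition is anticipated with certainty.

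- Day 4 only: shift in that condition's mean baseline = D/3.
- Half the shift also at Day 3: D/3 + (1/3)(D/2) = D/2.

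The documents give no value for D. Over an assumed range:

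| D (assumed) | Day 4 only | With half at Day 3 |
|---|---|---|
| 0.1 SD | 0.03 SD | 0.05 SD |
| 0.3 SD | 0.10 SD | 0.15 SD |
| 0.5 SD | 0.17 SD | 0.25 SD |

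Counterbalancing removes effects common to a visit position. It spreads this effect evenly over conditions, but does not cancel a shift that occurs in one condition and not in another.

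**5. Baselines as mediators.** With random order and a truly concealed condition, a same-day baseline cannot respond to the condition to come, apart from chance or carryover. A condition-to-baseline path in the model would therefore reflect chance, carryover or anticipation, and not a mechanism of the intervention.

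**6. Expectancy at post-test.** This needs no arithmetic and does not depend on Day 4. Under the article's own wording, concealment ends when the intervention begins. Post-intervention saliva, tasks and EEG all come later. Table 2 places achievement testing at 95–115 minutes, after the intervention, with no pre-intervention counterpart, so no achievement score is ever obtained under concealment.

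**7. Leaving out Day 4.** Both members of a given pair of conditions fall on Days 2 and 3 only when the third condition is last, in 2 of 6 orders. Complete within-child pairs fall from 103 to about 103 × 2/6 ≈ 34.

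**The case against.** Several points on the other side stand.

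- The statement that children are not informed can remain literally true at Day 4, since staff need say nothing. What cannot be assured is the clause on being unaware of the order.
- The content of the assent is not shown. That children know the set of three is an assumption, though a likely one.
- The article rests its expectancy claim on the control conditions and not on concealment, so predictability at Day 4 does not by itself overturn that claim. The claim fails on separate grounds: known condition at post-test, and no described matching or measurement of expected benefit.
- Predictability of the last period is inherent in any complete crossover with recognisable conditions, and analyses by period are commonly left to a fuller plan. What remains is that two statements in the article are stronger than the design allows.

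A reader might go further and infer that anticipation does distort the baselines, or that the exercise–rest comparison is biased by it. The documents support neither. They contain no data on anticipatory shifts. The argument given concerns anticipation of the TSST, and a shifted TSST baseline does not enter exercise versus rest. For the same reason the shifts computed above should not be measured against an effect planned for exercise versus rest. A reader might also want to base the conclusions on Days 2 and 3 if Day 4 baselines differ. That would let a preliminary test choose the main analysis, would leave about 34 complete pairs, and would still include Day 3, where the condition is already narrowed to two.

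**Conclusion.** The concern holds in limited form. The exclusion of expectancy effects is a property that the described design does not have, and this conclusion needs no assumption about what children were told. The unqualified statement that children are unaware of their order cannot be assured at Day 4 and is weakened at Day 3, provided they know the set of conditions. On that assumption one third of visits (103 of 309) are fully predictable before the baseline measures. The resulting distortion is possible but of unknown size: 0.03 to 0.17 SD in one condition's mean for an assumed shift of 0.1 to 0.5 SD at Day 4, or 0.05 to 0.25 SD if half the shift also occurs at Day 3. It bears mainly on contrasts involving the TSST and on any mediation reading of baseline sAA or cortisol.

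**What to change.** 1. In Summary of aims, remove expectancy effects from the factors that the design is said to exclude.
2. In Blinding and randomization, state that the upcoming condition is concealed on Day 2, partly concealed on Day 3 and not assured to be concealed on Day 4.
3. Report pre-intervention sAA, cortisol, task and EEG measures by upcoming condition and visit position. Do not read a condition-to-baseline path as mediation without this check.
4. Pre-specify, as a sensitivity analysis only, the condition contrasts without Day 4 visits. State that about 34 of 103 children then contribute both conditions of any given pair. The main analysis keeps all visits whatever the baseline table shows.

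The cost is two wording changes, one table and one additional analysis of data already being collected. The sensitivity analysis will be much less precise than the main one, so failure to reproduce a significant result in it should not be taken as evidence of anticipation.

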### Data monitoring

Access to individually identifiable private information will be restricted to the research coordinator, who will be the sole person responsible for maintaining that database. Identifiable and personal information will be kept separate from data, password-protected, and maintained in a secured room. All other individuals will be provided with only the unique record number assigned to each participant. All data will be protected via locked file cabinets or freezers behind locked doors, and password-protected personal computers located in [name] or [name] laboratories. Anonymized data will be entered into REDCap (Research Electronic Data Capture). REDCap is a secure web application for building and managing surveys and databases. It allows a streamlined process for rapidly creating and organizing databases and allows for automated exporting of data to Excel and common statistical packages (SPSS, SAS, Stata, R) as well as a built-in project calendar, a scheduling module, ad hoc reporting tools, and other features. Data quality is promoted through verification of the data entered into REDCap using outcome specific range restrictions. REDCap also has a sophisticated logging module allowing for the tracking of all entered data. No protocol amendments are anticipated at this time; however, protocol amendments will be approved by the Northeastern University Institutional Review Board before modifications are made.

### Power and analytic strategy

A traditional power analysis was conducted to estimate the appropriate sample size necessary for detecting a mediating effect of sAA levels on the relationship between a single bout of aerobic exercise and acute changes in cognition given the inclusion of potentially confounding variables (e.g., age, sex, BMI, IQ, SES) based on a one-sided alpha of .01 to correct for multiple outcomes and a power of 0.8. For the total effect of exercise on the ERP and cognitive outcomes, an effect size was calculated from the results reported in Hillman et al. [9], which observed increased P3 amplitude, task performance, and scholastic achievement following acute exercise relative to rest in a sample of preadolescent children resulting in a moderate-to-large effect size (Cohen’s *d* = 0.79). Therefore, assuming a medium size of Cohen’s *f*2 = 0.15 for the total effect and 8 predictors (including exercise condition, subject ID, and covariates) in the regression model, power analysis indicate that a sample size of 82 participants will provide adequate power to detect the effects of a single bout of exercise on neuroelectric function and behavioral performance. For the mediation analysis, medium effect sizes [33] were assumed for both the direct effect of exercise on sAA levels (path a: coefficient = a) and the direct effect of sAA level on the outcomes controlling for treatment condition (path b: coefficient = b). Corresponding to Cohen’s [34] criteria for medium (13% of the variance) effect size, the values of a and b were set at 0.39. Applying the Sobel [35] first-order test, the indirect effect or the mediated effect of exercise on outcomes through sAA was indicated by the product of a and b and was tested. Empirical power results [36] showed that a sample size of *N* = 103 per study was required to detect the presence of mediation. Accordingly, we aim to recruit *N* = 120 to account for attrition.

We will investigate whether the effect of the experimental conditions (*x*) on brain function, cognition, or academic achievement (distal *y* outcomes) is mediated by sAA and CORT baseline levels (*i*) and sAA change (*s*) using a path modeling framework (Mplus v8) and conventional model-to-data fit indices [37]. Each model will be adjusted for the set of potentially confounding variables (e.g., age, sex, BMI, IQ, SES). We will interpret significant direct effects on each outcome as supporting our hypotheses. We aim to incorporate the change process of sAA (*s*) and CORT (*s*) within the same model (allowing s and s to covary). We will utilize the most current and recommended practices [38, 39] for testing moderated mediation framework that leverages the stability of the entire sample for model estimation (causal structure); 5000 bootstrap draws will be run to collect the bias-corrected bootstrapped confidence intervals (95% CI) and significant indirect effects will be decomposed in Mplus output (identical to the Sobel test [35]). If mediation is found, subsequent tests of moderation will be conducted. To test the effect of the treatment condition (i.e., exercise, TSST-C, rest) on univariate continuous outcomes (brain function, cognition, academic achievement), three separate models will be tested using planned comparisons with imposed group invariance constraints. Group comparisons in sAA mean can be simultaneously compared (Is sAA larger in exercise compared to TSST-C and/or rest?), while also comparing benefits in the continuous outcomes regressed on sAA.

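### The 0.8 power stated for the mediation test does not follow from the article's own inputs: at one-sided alpha .01, N = 103 gives the Sobel test about 0.7

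*Protocol article*

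**What the plan says.** All of this is in the protocol article, *Power and analytic strategy*.

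- The first paragraph opens with a power analysis for detecting mediation by salivary alpha-amylase (sAA), "based on a one-sided alpha of .01 to correct for multiple outcomes and a power of 0.8". No other alpha is given for any sample size in that paragraph.
- For the total effect of exercise, it assumes f² = 0.15 and 8 predictors and states that "a sample size of 82 participants will provide adequate power".
- For mediation, it refers to "criteria for medium (13% of the variance) effect size" and says that "the values of a and b were set at 0.39". The test is given by "Applying the Sobel [35] first-order test" to the product of the two paths.
- The result is credited to a cited source: "Empirical power results [36] showed that a sample size of" "103 per study was required to detect the presence of mediation". Recruitment is then raised to "120 to account for attrition".
- The second paragraph says how mediation will be judged: 5000 bootstrap draws and a bias-corrected 95% confidence interval. It also describes the decomposition of indirect effects as equivalent to the Sobel test.

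**The concern.** The paragraph supplies everything needed to check the mediation sample size: alpha, sidedness, power, both path coefficients, their scale and the test. A first-order Sobel calculation on those inputs does not return 103 at the stated alpha. It comes very close to 103 at two-sided .05, which carries no correction for multiple outcomes.

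Mediation by sAA is the stated primary goal (*Background*) and the prediction under *Primary outcome*, and 103 is the larger of the two sample sizes. If the Sobel power is about 0.7, the chance of missing a true effect of the assumed size with that test is about 29 to 32%, not 20%. A reader who relies on the stated 0.8 at a corrected alpha would give a null Sobel result more weight than it deserves.

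**Working it through.** **Inputs from the article.** a = b = 0.39; power 0.80; one-sided alpha .01; first-order Sobel test; N = 103.

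**Scale of the coefficients.** With unit residual variance, 0.39 explains 0.39² / (1 + 0.39²) = 0.1521 / 1.1521 = 13.2% of variance, which matches the stated 13%. Read as a standardized coefficient, it would explain 0.39² = 15.2%. Unit variances are therefore used.

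**Assumption.** Observations are independent. The article gives no within-child correlation.

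**Closed form.** The Sobel z has approximate mean ab√N / √(a² + b²) = 0.39√(N/2). Hence N = 2 × ((z_alpha + 0.842) / 0.39)².

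| Alpha | z_alpha | N for power 0.80 | Power at N = 103 |
|---|---|---|---|
| two-sided .05 | 1.960 | 103.2 | 0.799 |
| one-sided .01 (stated) | 2.326 | 132.0 | 0.682 |
| two-sided .01 | 2.576 | 153.6 | 0.588 |

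At the stated alpha: 0.39 × √51.5 = 2.799; 2.799 − 2.326 = 0.472; Φ(0.472) = 0.68.

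**Simulation of the same Sobel test** (normal exposure, no direct effect, unit residual variances). Power is higher here because the simulated statistic varies less than a standard normal.

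| N | two-sided .05 | one-sided .01 |
|---|---|---|
| 90 | 0.80 | 0.59 |
| 103 | 0.88 | 0.71 |
| 115 | 0.93 | 0.80 |
| 120 | 0.94 | 0.83 |

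Other exposure codings and a non-zero direct effect, still with unit residual variance and an exposure variance of 1, give 0.71 to 0.73 at N = 103 and one-sided .01. The stated 0.80 is missed by both methods. The match to two-sided .05 holds for the closed form only; by simulation that level needs about 90.

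**Cross-check on 82.** Single-coefficient test, f² = 0.15, 8 predictors, df = N − 9, noncentrality √(0.15N):

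- two-sided .01: power 0.797 at N = 81 and 0.803 at N = 82, so N = 82;
- one-sided .01: power 0.793 at N = 69 and 0.800 at N = 70, so N = 70.

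The stated 82 fits two-sided .01, not the stated one-sided .01.

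**Planned test.** A bias-corrected bootstrap of ab at N = 103, under the same model, gives about 0.90 to 0.93 across separate simulation runs at one-sided .01 (a 98% interval), and about 0.96 to 0.97 for the planned 95% interval.

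**The case against.** Five arguments weigh against the point.

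- **The planned test is not the Sobel test.** Mediation will be judged by a bias-corrected bootstrap interval, and under the article's own assumptions that test exceeds 0.8 at N = 103 even at one-sided .01. This stands. A reader might infer from the Sobel shortfall that the trial is underpowered for mediation; the article does not support that. What remains wrong is the power statement, which names a different test and a different level from the analysis.
- **The 103 comes from cited empirical results.** This also stands as far as origin goes. A reader might infer that 103 simply is the two-sided .05 Sobel size. The closed form agrees to within rounding (103.2), but simulation of the same test at that level needs only about 90, and the source is not shown. The shortfall at the stated alpha does not depend on where 103 came from.
- **0.39 could be a standardized coefficient.** It would then explain 15.2% of variance, against the stated 13%. Simulated power at 103 and one-sided .01 is then 0.775. It reaches 0.805 only if a direct effect of 0.14, which the article never mentions, is added.
- **120 will be recruited.** With all 120 analysable, power at one-sided .01 would be 0.76 (closed form) or 0.83 to 0.85 (simulation). But the 120 is there to absorb attrition, so 103 is the number being powered.
- **The trial is a crossover.** Each child completes all three conditions, so repeated measurement could change the true power. No within-child correlation is given, so the size of that change cannot be derived. The check therefore tests the article's stated calculation, not the power this design will actually have.

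The mismatch for 82 does no harm by itself: 82 exceeds 70 and is not the binding number.

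**Conclusion.** The point holds for the stated calculation. At one-sided alpha .01, with a = b = 0.39, unit residual variances and independent observations, the first-order Sobel test at N = 103 has power of about 0.68 to 0.71, not 0.80. The N for 0.80 is about 132 by closed form or about 115 by simulation. The 82 fits two-sided .01 and the 103 fits two-sided .05 in closed form, so the stated alpha appears not to have been applied consistently. That explanation of the 103 remains an inference.

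The severity is moderate. A stated power for the primary hypothesis is wrong as written, and the level of the planned interval (95%) does not match the one-sided .01 said to correct for multiple outcomes. Neither fact shows that the planned bootstrap test lacks power. The bootstrap figures rest on the same independence assumption and on the interval holding its nominal level, which was not checked.

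**What to change.** Revise *Power and analytic strategy* as follows.

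1. Give the alpha and sidedness beside both 82 and 103.
2. Then choose one of two routes:
   - keep the Sobel calculation and state that 103 analysable children give power of about 0.7 at one-sided .01, and about 0.8 by closed form only at two-sided .05; or
   - base the power statement on the planned bias-corrected bootstrap and align the interval with the stated alpha (a 98% interval for one-sided .01). Under the same assumptions this gives about 0.90 to 0.93 at N = 103.
3. With either route, say that the figure treats observations as independent, or give the within-child correlation assumed.

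The cost is a rewritten paragraph and, for the second route, a short simulation. No extra children are needed. The first route makes the published power figure less favourable; the second widens the mediation interval from 95% to 98%.

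### Path b of the mediation model, as described, is not restricted to within-child variation, so stable child differences in sAA reactivity can pass for mediation

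*Protocol article*

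**What the plan says.** The Summary of aims and Primary outcome sections predict that exercise-induced phasic increases in sAA mediate the effect of a single bout on P3, executive control and achievement. Under Interventions, the crossover is justified because "participants will act as their own controls".

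Under Power and analytic strategy, path a is the effect of exercise on sAA and path b is "the direct effect of sAA level on the outcomes controlling for treatment condition". For sample size, "the values of a and b were set at 0.39", and the product is tested by "Applying the Sobel [35] first-order test".

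The analysis paragraph of that section describes an Mplus path model in which condition acts through baseline sAA and cortisol (i) and sAA change (s), with a 95% bias-corrected bootstrap interval for the indirect effect. On adjustment it says "Each model will be adjusted for the set of potentially confounding variables (e.g., age, sex, BMI, IQ, SES". Conditions are compared as groups under invariance constraints, "while also comparing benefits in the continuous outcomes regressed on sAA". Subject ID is named once, as one of 8 predictors in the total-effect power calculation. No child effect, two-level structure or child-mean centring is described for the mediation path.

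**The concern.** Randomising the order of conditions protects path a, because each child's sAA under exercise is compared with the same child's sAA under rest. It does not protect path b, because sAA response is not randomised. A slope of outcome on sAA change, given condition, combines two questions: whether a child does better in the session where his or her own sAA rose more, and whether children who generally react more also generally do better. Only the first is the stated hypothesis.

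Mediation by sAA is the primary goal, and the Discussion expects exercise to raise sAA, so path a is likely to be non-zero. The mediation conclusion then rests largely on path b. A positive stable correlation between reactivity and outcome could be reported as a mechanism; a negative one could hide a real mechanism.

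The listed covariates remove only what they measure. The Discussion also expects performance to differ by fitness, which is not among the covariates named.

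**Working it through.** **1. The plan's own figure.** With a = b = 0.39 and standard errors of 1/√N, the Sobel statistic is 0.39·√(N/2), so N = 2·((z_α + z_power)/0.39)².

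- Two-sided 0.05: 2·((1.960 + 0.842)/0.39)² = 103.2.
- One-sided 0.01, as stated ("based on a one-sided alpha of .01 to correct for multiple outcomes and a power of 0.8"): 2·((2.326 + 0.842)/0.39)² = 132.

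The stated 103 is reproduced at two-sided 0.05. The alpha mismatch is a separate matter. What matters here is that the formula reaching 103 uses one slope b over N independent observations, with no split into within-child and between-child parts.

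**2. What the uncentred slope estimates.** Let λ be the share of sAA-change variance (given condition) that is stable child reactivity, κ the share of outcome variance that is stable in the child, and ρ their correlation. In SD units,

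slope = b_within + ρ·√(λκ).

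The article gives none of these. Assume λ = 0.30 and κ = 0.50, so √(0.30 × 0.50) = 0.387. With b_within = 0, the slope is 0.077, 0.116 and 0.194 at ρ = 0.2, 0.3 and 0.5. Simulated mean slopes were 0.076, 0.111 and 0.184. Centring sAA change on the child's mean removes the second term.

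**3. False-mediation rates.** Simulated: 103 children × 3 conditions, true b_within = 0, a = 0.78 SD, i and s both entered, five child-level covariates, and subject ID as one numeric predictor. The test was a Sobel test with child-clustered standard errors, in place of the planned bootstrap.

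| Assumed ρ | Post-only outcome, 95% | Post-only, one-sided 0.01 | Change outcome*, 95% |
|---|---|---|---|
| 0 | 5.8% | 0.8% | 5.6% |
| 0.2 | 19.5% | 10.2% | – |
| 0.3 | 37.6% | 24.8% | 18.4% |
| 0.5 | 78.0% | 67.2% | 37.6% |

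*Here ρ is the correlation of reactivity with a stable tendency to improve. If reactivity correlates only with stable ability, the change outcome gives 4.3–5.8%.

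A second simulation of this design, also with assumed variance shares, gave about 21%, 43% and 83% (post-only) and 12%, 21% and 52% (change) at 0.2, 0.3 and 0.5.

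With child-mean-centred sAA change, the first simulation gave 3.8–5.2% at the 95% criterion and 0.6–1.2% at one-sided 0.01 in every scenario.

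**4. Power after centring.** With a = b = 0.39, power is 0.82 centred against 0.78 uncentred at one-sided 0.01, and 0.90 against 0.89 at the 95% criterion.

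**The case against.** The strongest reply is that the path b sentence is a power assumption, not the analysis. A reader might infer from it that path b controls only for condition and fixed child covariates, so that any stable link between sAA level and ability creates mediation. Such a model would give 28.2% and 65.8% false mediation at correlations of 0.3 and 0.5. The article does not support that reading: the analysis enters baseline (i) as well as change (s), and with both in the model, level confounding alone gives 4.9–5.8%.

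The Primary outcome section also describes outcomes as changes, and cognitive and EEG tasks are run before and after each intervention. That removes stable ability from those outcomes and leaves the narrower route through a stable tendency to improve. It does not help the WRAT-4, which is given only after the intervention.

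A reader might also infer that a between-child association is to be expected, because the Summary of aims says "Phasic sAA has been shown to be related with attention, memory, and various academic outcomes". That sentence does not say whether the relations are between or within children, so it cannot establish a non-zero correlation. It does not support assuming zero either.

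Finally, the article does not state that the model is single-level, and a fuller plan may specify two levels. That stands. But the article does name the mediators, adjustment set, software, bootstrap and group constraints, and these together describe a path b that does not isolate the hypothesised effect. A single subject-ID term, even if carried over from the total-effect regression, did not prevent the inflation above.

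**Conclusion.** The point holds in a limited form. As described, path b mixes within-child and between-child association, while the hypothesis and the design are within-child. Baseline plus change deals with stable sAA level; stable sAA reactivity remains. Exposure is greatest for the WRAT-4. For EEG and cognition as pre-post change it is conditional on reactivity being linked to a stable tendency to improve.

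The rates rest on assumed variance shares and correlations and on a clustered Sobel test. They show what could happen at given correlations, not what the trial should expect. At zero correlation, the test is near nominal. The change is worth making because the primary conclusion depends on path b and the remedy is only a matter of specification.

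**What to change.** Define the mediated effect as a × b_within. In Mplus, use a two-level or child-mean-centred path model that splits sAA change into the child's mean over sessions and the session's deviation from it, and treat cortisol change the same way. Bootstrap whole children. Base the mediation conclusion on the within-child product and report the between-child slope as descriptive. A random child intercept without centring is not enough, because uncentred sAA still mixes the two slopes.

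Regressing the exercise-minus-rest outcome difference on the matching sAA difference is an alternative, but it drops the TSST session and is not equivalent to the three-session model.

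For the WRAT-4, each child is tested after rest and after either exercise or TSST. Only those tested after both rest and exercise inform the exercise–rest within-child contrast: about 51 of 103 if the split were even, which the article does not state. Precision there will be lower, and the plan should say so.

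The cost is wording and model specification, with no new data. Path b would use only within-child variation. Power did not fall at a = b = 0.39, but a modest loss is possible where there is no between-child confounding. A simpler simulation with one mediator and no baseline term (a = 0.8, b = 0.2, zero correlation) gave 81–83% within-child, against 93–95% with a random intercept and 80–92% pooled. Centring removes stable child differences only; factors that vary between sessions can still confound path b.
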